#### Main outcome variables

- Fibromyalgia Impact Questionnaire (FIQ) [25]: The FIQ is a 10-item self-report questionnaire developed to measure the health status of FM patients. The first item focuses on the patient's ability to carry out muscular activities. In the next two items, patients are asked to circle the number of days in the past week they felt good and how often they missed work. Finally, the last seven questions (job ability, pain, fatigue, morning tiredness, stiffness, anxiety and depression) are measured by a visual analogue scale (VAS). The Spanish validated version will be used [26].

- Pain Visual Analogue Scale (PVAS): The PVAS was designed to allow a thorough and understandable subjective assessment of pain. A Visual Analogue Scale is usually a 10-cm horizontal line, with perpendicular lines on the edges, defined as the extreme limits of pain experience. Anchoring points at each edge are characterised by verbal expressions such as "No pain" (accompanied by the number "0") at one end and "maximum pain ever experienced" (accompanied by the number "100") at the other end. The adequate psychometric properties of PVAS have been demonstrated in previous studies [27,28]. The Spanish validated version of this questionnaire will be used [29].

- Pain threshold assessed by sphygmomanometer: the sphygmomanometer, a universally used clinical test, has been demonstrated to be helpful in the identification of patients with FM [30]. It has been recommended that the blood pressure cuff be inflated at an approximate rate of 10 mm Hg per second up to 180 mm Hg or to the point where pain is elicited. Healthy persons usually experience pain when the blood pressure cuff is inflated to 160 mm Hg or more; however, patients with FM usually experience pain at 100-110 mm Hg or at even lower pressure [30].

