##### Other variables

- Psychiatric diagnosis: This will be performed with the MINI psychiatric interview [37], a psychiatric interview developed by our group and extensively used for the study of psychiatric disorders in primary care. It allows the use of DSM-IV diagnostic criteria. We specifically assess the presence of Post-traumatic Stress Disorders because it seems to be associated with a worse prognosis [38].

- Hospital Anxiety Depression Scale (HADS): This is a self-reported scale designed to screen for the presence of depression and anxiety disorders in medically ill patients. It contains 14 items rated on four-point Likert-type scales. Two subscales assess depression and anxiety independently (HADS-Dep and HADS-Anx, respectively) [39]. Patients with 14 or more points in the complete scale (or more than eight in either of the two subscales) are considered "probable cases" of anxiety and/or depression. The validated Spanish version of this questionnaire will be used [40].

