#### Analysis strategy

At baseline, means and standard deviations will be calculated for continuous variables in the study in case of normality, or medians and interquartile periods where this hypothesis is not fulfilled. The Kolmogorov-Smirnov test will be applied to ensure the adjustment of data to a normal distribution.

The existence of differences in socio-demographic, main outcome and other variables regarding pain-related psychological constructs will be analysed. These differences will be studied using Chi Square test for qualitative variables, with the Fisher test being utilized when necessary. To determine the relationship between categorical variables with one or two levels and quantitative variables, Student T test or variance analysis will be used, respectively, for variables fulfilling the normality hypothesis. For the remaining variables, non-parametric tests such as Man-Whitney U or Kruskall-Wallis will be used. To assess the predictive value of pain-related psychological construct on main outcome variables at one-year follow-up, use will be made of a logistic regression analysis adjusted for socio-demographic and clinical variables.

A Spearman Rho non-parametric correlation matrix will be developed to determine the relationship between pain-related psychological constructs and possible overlapping, including these constructs and the other variables, for the analysis of the significance of this matrix and each one of the calculated correlations. Patients will be grouped according to pain-related psychological constructs using cluster analysis, with a profile graph to represent the results of this multivariant analysis. Data will be analysed using the SPSS 15 statistical package.

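### Logistic regression is planned for three one-year outcomes that are all quantitative and have no stated cut-off, so grouping the scores would discard information

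*Protocol article*

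**What the plan says.** The Analysis strategy section of the protocol article sets the goal "To assess the predictive value of pain-related psychological construct on main outcome variables at one-year follow-up" and names the model: "use will be made of a logistic regression analysis adjusted for socio-demographic and clinical variables".

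The Main outcome variables section describes the three outcomes that this model has to take:

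- FIQ: "The FIQ is a 10-item self-report questionnaire developed to measure the health status of FM patients". Seven of its items are visual analogue scales.
- Pain VAS: "A Visual Analogue Scale is usually a 10-cm horizontal line", with ends labelled 0 and 100.
- Pain threshold: a cuff "inflated at an approximate rate of 10 mm Hg per second up to 180 mm Hg or to the point where pain is elicited", so a reading in mm Hg with an upper limit.

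No responder or case definition is attached to any of the three. The values of 160 and 100-110 mm Hg in the same section describe what healthy people and FM patients usually report; they are not set as outcome classes. The only case cut-off in the article is for the HADS (Other variables): "Patients with 14 or more points in the complete scale (or more than eight in either of the two subscales". By Table 1 the HADS is a baseline-only measure, and it is not a main outcome.

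**The concern.** A model for categorical outcomes has been fixed for outcomes measured on quantitative scales, and the article does not say how one becomes the other. The rest of the Analysis strategy section treats quantitative variables as such, with means, t tests, analysis of variance and Spearman correlations.

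This regression is the only analysis named for the one-year outcomes, so what the study can say about prognosis depends on it. If each score is split in two, patients just either side of the cut count as opposite outcomes, while patients far apart on the same side count as equal. A construct's odds ratio then depends on where the cut falls, and small to moderate associations are harder to detect or to rank. Ranking matters here because the general aim concerns how important the constructs are for function and pain.

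**Working it through.** **Inputs.** From the article: n = 305 (Sample size), three quantitative outcomes without cut-offs, and logistic regression as the model. Assumed, because the article gives none of these: an approximately normal outcome, a small effect, a binary split between 50/50 and 80/20, and effect sizes r from 0.16 to 0.30.

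**The plan's own figure.** The article gives no power or precision figure for this regression. Its 305 comes from a formula for estimating a proportion. With 95% confidence, p = 0.5 and N = 30,000, that formula gives 380 at a 5% error and 1,031 at 3%, so 305 does not reproduce. That is a separate matter; 305 is used below only as the planned number of patients.

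**Step 1: information kept after a binary split.** For a normal outcome cut at quantile q and a small effect, efficiency relative to the uncut score is φ(z_q)² / [q(1 − q)].

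| Split | φ(z_q) | Calculation | Efficiency | Loss | 305 × efficiency |
|---|---|---|---|---|---|
| 50/50 | 0.3989 | 0.3989² / 0.25 | 0.637 | 36% | 194 |
| 70/30 | 0.3477 | 0.3477² / 0.21 | 0.576 | 42% | 176 |
| 80/20 | 0.2800 | 0.2800² / 0.16 | 0.490 | 51% | 149 |

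**Step 2: smallest detectable correlation** (80% power, two-sided 5%): r = tanh[(1.960 + 0.842) / √(n − 3)].

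- Continuous score, n = 305: tanh(2.802 / √302) = 0.16
- Median split, effective n = 194: tanh(2.802 / √191) = 0.20
- 80/20 split, effective n = 149: tanh(2.802 / √146) = 0.23

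**Step 3: simulated power**, n = 305, normal outcome, no prognostic covariate, 1,500 runs:

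| r | Linear | Logistic 50/50 | Logistic 70/30 | Logistic 80/20 |
|---|---|---|---|---|
| 0.16 | 80% | 61% | 58% | 50% |
| 0.20 | 94% | 81% | 77% | 71% |
| 0.25 | 99% | 94% | 91% | 86% |
| 0.30 | 100% | 99% | 98% | 96% |

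Separate simulations at r = 0.16 gave 62% at the median split, 54% at 70/30 and 50-51% at 80/20, so 50-62% is a fair range for that effect.

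**Step 4: effect of a strong covariate.** With a covariate that explains an assumed 36% of outcome variance and a partial r of 0.16, simulated efficiency was 0.50 at the median split and 0.38 at 80/20, a loss of 50% to 62%. Power was 80-81% with linear regression, against 52% and 41% with logistic. The Step 1 losses are therefore not the worst case when adjustment is strong.

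**The case against.** The strongest reply is that this is a condensed article and that the full protocol or analysis plan may define cut-offs. A reader might infer from the article's silence that the cuts would be chosen after the data are seen, perhaps to favour a result. The document does not support that: nothing in it says when or how cuts would be set, and such detail is often left to a fuller plan. This part of the reply stands, and the point here does not rest on that inference. Cut-offs fixed elsewhere would settle the choice of cut but would leave the loss of information and the dependence on the cut.

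Second, logistic regression need not be binary. An ordinal model would lose less. It is not mentioned, however, and grouping the scores for it would still require category limits.

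Third, the size is conditional. A reader might take 36-51% as a property of this study, but normality, a small effect and the range of splits are all assumptions. The Analysis strategy section itself allows for non-normal variables, and cuff readings stop at 180 mm Hg. The power gap also narrows as effects grow: at r = 0.30 it is at most 4 percentage points (100% against 96%). Precision is lost even where power is not.

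Fourth, it would be too much to say that the general aim rests on this model alone. The same section also compares main outcome variables in relation to the constructs using t tests, analysis of variance or rank tests, which keep scores quantitative. The logistic model is the one-year predictive analysis only.

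Finally, with a pre-set cut, binary logistic regression is inefficient rather than invalid. That is correct.

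**Conclusion.** The point holds as a poor choice of model stated in the text, not as a missing detail. The article assigns logistic regression to three quantitative one-year outcomes, and nothing in it resolves the mismatch. For a roughly normal outcome, a small effect and a binary split, the cost is about 36% of the information at the median, 42% at 70/30 and 51% at 80/20. More extreme cuts or strong covariates increase it; an ordinal model would reduce it. In power terms the cost is large at r = 0.16 (about 80% down to 50-62%), moderate at r = 0.25 (about 99% down to 86-94%) and small at r = 0.30. The article gives no effect size, so no single one of these can be called the expected loss.

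**What to change.** In the Analysis strategy section, make the main one-year predictive analysis a multiple linear regression of each outcome (FIQ, pain VAS, pain threshold) as a continuous score. Adjust each model for that outcome's own baseline value, which Table 1 and the Procedure section show is already collected, together with the planned socio-demographic and clinical variables. Report coefficients with 95% confidence intervals.

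Use robust standard errors if residuals are skewed. They do not deal with readings that stop at the 180 mm Hg limit. If many do, use a censored (Tobit) or ordinal model for the pain threshold.

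Keep logistic regression only as a secondary analysis, with each cut-off and its source fixed in advance.

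The cost is a change of wording, with no additional patients, visits or measurements. The small downside is that results are score differences rather than odds ratios.

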- *Mindfulness: *This concept is defined as the practice of being mindful, focused on the present moment and without judging the situation we have to live through [20]. It has been demonstrated that mindfulness correlates positively with several measures of psychological well-being and that it is associated with significant long-term improvement in patients with pain and, specifically, in FM [20,21].

- *Positive and negative affect: *Affect has been described as the observable expression of emotion, which can be both positive and negative [22,23]. Negative affect has been related with poor outcomes in FM [22,23], but recently the emphasis has been put on the affect balance style (relative levels of negative and positive affect) as a prognostic marker in FM [24].

It is not currently known whether these psychological constructs correlate between themselves or even overlap each other. In addition, their specific significance for prognosis and treatment on chronic pain disorders has not been assessed. The general aim of this study is to assess the importance of pain-related psychological constructs on function and pain in patients with FM. The specific objective is to assess correlations and possible overlapping among constructs.

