- Perceived injustice: a 12-item self-report measure, the Injustice Experience Questionnaire (IEQ) [19], was developed to measure this concept. It addresses the degree to which individuals perceive their post-disorder life as being characterized by injustice. Principal component analysis yielded a two-component solution. These factors were labelled "irreparability of loss" and "blame/unfairness". The psychometric properties of IEQ are considered adequate. We will validate a Spanish version of this test on an independent sample to be used in the study.

- Mindfulness: Several questionnaires have been used to assess the concept of mindfulness. For this study we will use one of the most widely used, the Mindful Attention Awareness Scale [21]. This is a 15-item self-administered questionnaire. Principal component analysis yielded a one-factor solution. The respondents indicate how frequently they have the experience described in each statement using a 6-point Likert scale from 1 (*almost always*) to 6 (*almost never*), where high scores reflect more mindfulness. In an attempt to monitor for socially-desirable responses, respondents are asked to answer according to what "really reflects" their experience rather than what they think their experience should be. The items are distributed across cognitive, emotional, physical, interpersonal and general domains. Psychometric properties of the questionnaire are adequate [21]. A Spanish version of this test will be validated on an independent sample to be used in the study.

-Positive and Negative Affect: This will be measured with the Positive and Negative Affect Scale (PANAS) [35]. The PANAS consists of 2 mood scales with 10 items each for the assessment of PA and NA. Scores for each scale range from 0 to 50. The scales have been shown to be internally consistent, uncorrelated and stable over a 2-month period; good convergent and discriminant validity have also been demonstrated [35]. The Spanish validated version will be used [36].

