### Statistical methods

#### Sample size

To calculate the sample size, it is necessary to know the population that suffers from FM in the region of Aragon. According to epidemiological studies [2] the prevalence of FM in Spain is 2-3%. The population of Aragon is calculated at 1,250,000 inhabitants, and based on this prevalence data the number of persons diagnosed with FM could be 30,000 patients. With a confidence level of 95%, an estimated error of 5% and considering the most unfavourable assumption (*p *= 0.5), a sample of 305 patients will be necessary, using an accuracy of 3%. EPIDAT 3.1 was used to calculate the sample size.

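### The overlap part of the specific objective is read only through the significance of Spearman correlations, which shows association but cannot separate related constructs from redundant ones

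*Protocol article*

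**What the plan says.** The last paragraph of the Background in the protocol article states: "The specific objective is to assess correlations and possible overlapping among constructs". Just before this it says that two things are unknown: whether the constructs correlate, and whether they go as far as overlapping. The authors thus treat overlap as something more than correlation.

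The Analysis strategy section answers with one method: "A Spearman Rho non-parametric correlation matrix will be developed to determine the relationship between pain-related psychological constructs and possible overlapping". The sentence then widens the matrix to the other study variables and says what it is for: "for the analysis of the significance of this matrix and each one of the calculated correlations". It gives no size of correlation that would count as overlap, no null value and no alpha level.

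One other multivariate method is named: "Patients will be grouped according to pain-related psychological constructs using cluster analysis". It sorts patients, not scales. The logistic regression in the same section concerns outcome at one year.

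**The concern.** The significance of a correlation ordinarily means a test that it differs from zero. Rejecting that null shows that two scales are associated. It does not show that they measure the same thing. Pain-related constructs in one patient group can be expected to be at least weakly related, so a test against zero will tend to give the same answer for weakly related pairs and for near-duplicates.

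At stake is the claim that, say, catastrophizing and mental defeat are distinct or redundant. If significance is the only reading, that claim has no support from the named analysis. If a cut-off on size is chosen after the matrix has been seen, the conclusion depends on the data that suggested it.

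**Working it through.** **Inputs**
- n = 305, from the Sample size section.
- Construct scores: catastrophizing, acceptance, mental defeat, inflexibility, injustice and mindfulness, plus two for affect ("The PANAS consists of 2 mood scales with 10 items each for the assessment of PA and NA"). That is 8 scores and 8 × 7 / 2 = 28 pairs, or 7 × 6 / 2 = 21 if affect is one score.
- Two-sided alpha 0.05 and a null of zero: assumed, as neither is stated.

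**The plan's own figure.** The article gives no figure for the correlation analysis; 305 comes from a precision formula for one proportion. With 95% confidence, p = 0.5 and a population of 30,000:
- 5% error: n0 = 1.96² × 0.25 / 0.05² = 384.1; corrected, 384.1 / (1 + 383.1/30,000) = 379.3, so 380.
- 3% error: n0 = 1,067.1; corrected 1,030.5, so 1,031.

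Neither gives 305. That is a separate matter, and the sensitivity check below shows that this point does not depend on it.

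**Smallest significant correlation.** |rho| = t / √(n − 2 + t²).
- n = 305: t = 1.968, so 1.968 / √(303 + 3.87) = 0.112; squared, 0.0126, or 1.3% shared rank variance.
- Bonferroni over 28 pairs: t = 3.152, so 3.152 / √(303 + 9.93) = 0.178, or 3.2%.

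**Sensitivity to n.** The construct scales are given only at baseline (Table 1), so loss to follow-up does not touch the matrix. Under-recruitment or incomplete questionnaires could.
- 20% or 30% fewer patients (assumed; n = 244 or 214): 0.126 or 0.134.
- n = 380: 1.966 / √(378 + 3.87) = 0.101.
- n = 1,031: 1.962 / √(1,029 + 3.85) = 0.061.

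**Chance of significance at n = 305.** Fisher z with the Spearman variance, SE = √((1 + rho²/2)/(n − 3)); power = Φ(atanh(rho)/SE − 1.96).
- rho = 0.2 (4% shared rank variance): 0.2027 / 0.0581 − 1.96 = 1.53, so 93.7%.
- rho = 0.3 (9%): 0.3095 / 0.0588 − 1.96 = 3.30, so 99.95%.
- rho = 0.9 (81%): practically 100%.

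**What the coefficients themselves can show.** 95% limits: tanh(atanh(rho) ± 1.96 SE), n = 305.

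| Observed rho | 95% interval |
|---|---|
| 0.30 | 0.19 to 0.40 |
| 0.70 | 0.63 to 0.76 |
| 0.80 | 0.75 to 0.84 |
| 0.85 | 0.81 to 0.88 |
| 0.90 | 0.87 to 0.92 |

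Take a bound of 0.80 purely as an illustration. An observed 0.70 would lie clearly below it, 0.85 clearly above it, and 0.80 would be undetermined. The planned sample supports a criterion based on size; the test against zero does not use that information.

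**The case against.** No sentence says that a significant p-value means overlap, and none states a null of zero. A correlation matrix is first a table of coefficients, and any reader sees 0.15 and 0.85 as different whatever their p-values. Cut-offs, intervals and alpha are often left to a fuller plan, which is not shown and may contain them.

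Much of this stands. The null of zero is the ordinary reading, not quoted text, and a missing cut-off alone would be detail that an article may leave out. What remains is that the article does name how the matrix is to be read. It names significance, which does not fit the overlap question, and nothing else in the section fills the gap.

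Three stronger readings are tempting but not supported:
- *The specific objective as a whole would go unanswered.* It has two parts, and the matrix answers the correlation part directly.
- *The study cannot assess overlap.* The coefficients will be produced, and the intervals above show usable precision.
- *Multiple testing is the problem.* With 28 tests at 0.05, 28 × 0.05 = 1.4 false positives are expected only if all pairs are unrelated, which is hardly the practical worry with these constructs. The article also says nothing either way on adjustment. Bonferroni moves the threshold only from 0.112 to 0.178, so adjusting alpha would not repair the criterion.

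**Conclusion.** The point holds for the overlap part of the objective. The only reading named for the matrix separates rho from zero at about 0.112 (1.3% shared rank variance) with 305 patients, so pairs sharing 4% and 81% of rank variance would nearly always both be called significant. This rests on a null of zero and two-sided 0.05, both assumed. It does not rest on the exact sample size: the threshold stays at or below 0.134 from 214 patients upward. The correlation part of the objective is answered, and the data to be collected can also answer the overlap part once a criterion based on size is fixed. This is a mismatch of method and question that should be put right before analysis; it does not undermine the design.

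**What to change.** In the Analysis strategy section, state that overlap will be judged by the size of the correlation and not by its p-value. In detail:
- Report rho for each construct pair with its 95% confidence interval, using the Spearman variance.
- Work with absolute values, because acceptance and mindfulness are scored so that higher is better and may correlate negatively with the other scales.
- Fix a bound before the data are seen. Declare overlap only if the lower limit of |rho| exceeds it, distinctness only if the upper limit lies below it, and otherwise report the pair as undetermined.
- Do not call a pair overlapping merely because its interval reaches the bound. That rewards imprecision, since a smaller sample widens the interval and yields more overlap.
- Give a reliability-corrected value as a supplement only. With reliabilities of 0.8 (assumed), an observed 0.70 becomes 0.70 / √(0.8 × 0.8) = 0.875. The correction was derived for product-moment correlations, and reliability may differ between scales.
- A factor analysis of the subscale scores is optional.

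The scales are already scheduled at baseline, so no patients or visits are added. The cost is a little more analysis, item responses kept if reliability is to be estimated, and the investigators' commitment to a bound beforehand.
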